### Exclusion criteria

Inability to give informed consent, if under guardianship or a minorNeuromuscular diseaseDementiaHistory of upper limb surgery or pathologies that would make it impossible to fit electromyography (EMG) electrodes and measure handgrip forceEstimated life expectancy of less than 3 monthsHospitalization in the 3 months prior to the testParticipation in another clinical interventional trialAcute kidney diseaseWaitlisted for renal replacement therapy or expected to start dialysis within 3 monthsHistory or evidence of any other clinically significant disorder, condition or disease that in the investigator’s opinion could pose a risk to a participant’s safety or interfere with the study’s evaluation, procedures or completion

### Inclusion modalities

Participants will be informed about the study with a poster displayed in hospital or during medical consultations. Elderly CKD patients will be enrolled via the UIRAV unit. Control subjects will be enrolled through endocrinology, diabetology and dermatology units or during outpatient consultations with patients’ escorts.

### Materials

The handgrip and EMG evaluations will be synchronized using Labview v19 software (National Instruments Corp., Austin TX, USA) that makes it possible to simultaneously display feedback on strength and EMG activity. The handgrip dynamometer used will be the K-Force GRIP (K-Invent Inc., Montpellier, France), with 1000 Hz acquisition frequency and an accuracy of 100 g. The EMG signal will be recorded using the Trigno Wireless Biofeedback System (DelSys Inc., Boston MA, USA) with the Trigno Avanti™ electrodes, which are composed of a 4 silver bar contacts, 10 mm interelectrode, a 1926 Hz acquisition frequency per channel and with a second-order band-pass Butterworth filter set at 20–450 Hz and a second-order low-pass filter set at 100 Hz.

### Intervention

The patient being tested will be seated, with his back in a straight position, and elbow bent at 90° close to his chest. The patient’s humerus will be vertical and his forearm will be parallel to a height-adjustable support (Fig. 3). The patient’s dominant arm will be chosen.

**Fig. 3 Fig3:**
[figure not shown]
Set-up of the study and standardized position

Preparing the arm for placement of the electrodes will include shaving the skin and cleaning the area hosting the four recording electrodes [43, 44] with a sponge and alcoholic disinfectant to reduce impedance. Electrodes will be placed over the flexor digitorum superficialis muscle belly along the fiber direction while following international SENIAM recommendations and the four electrode positions previously described [43–45].

The exercise, illustrated in Fig. 2, will begin with a warm-up, to familiarize the person with the instruments and situation, at a slow and comfortable pace not exceeding 1 min and 30 sec. The warm-up will consist of dynamic extensions of the hand and fingers: an extension at maximum speed, and a slow and constant flexion of the wrist and fingers. Dynamic stretches have been shown to prepare the nervous system, increase muscle temperature and improve the sensitivity of the connecting bridges between actin and myosin [46] compared to passive stretches, which can be somewhat deleterious in terms of muscle performance [47].

According to the recommendations of Maffiuletti et al. [48], fast sub-maximum contractions (FSC) should be separated from MVC to limit central inhibition. Thus, to determine the baseline FSC, five contractions at maximum speed will be performed with a twenty-second rest interval between them. The objective of these contractions is to determine the rate of force development.

As recommended by De Luca [49], patients will perform three MVC interspersed by a two-minute rest and the mean of the three contractions will be calculated. Each MVC has to be reached progressively in less than 3 sec and least 5 sec [50]. A five-minute break is scheduled after the MVC because the subsequent part of the trial is the beginning of the fatigability protocol.

The fatigability assessment phase begins with nine contractions at 40% of MVC [51], each lasting 3 sec, followed by an FSC and an MVC. All the contractions are exerted at two-second intervals. This cycle of eleven contractions will be repeated six times. If a patient cannot maintain the 40% required force, the threshold time will be recorded without stopping the test. At the end of these cycles, the patient will rest for 1 min. Then, in order to assess their recovery capacities, the last part of the test will be administered, consisting in three series of one FSC and one MVC, separated by two- and three-minute intervals, respectively.

### Statistical analysis

Sample size calculation was based on the results of the handgrip strength test of Lin et al. [52], who analyzed a relatively large cohort of elderly patients suffering from CKD in 2019, and the handgrip strength reference values of Ramírez-Vélez et al. [36], who analyzed a larger population of elderly patients without CKD, stratified by age and sex. With an 8% (±16%) difference, accepting a 5% alpha risk, 96% statistical power will be reached by enrolling 110 CKD patients and 110 control subjects. Considering the number of patients followed in the UIRAV unit (i.e., approximately 180 older than 60), we should be able to enroll the participants within 1 year.

Signal filtering and analysis will be performed with Matlab 2018a v9.4 (The MathWorks Inc., Natick MA, USA) and statistical analysis will be performed with SPSS v14 (IBM Corp., Armonk NY, USA). Group comparison for normally distributed variables will be assessed by means of the analysis of variance (ANOVA) or the unpaired Student T-Test. For non-normally distributed variables the Kruskal-Wallis or the Mann-Whitney Test will be used. In addition, the chronological variables (e.g., evolution of the MVC during the test) will be analyzed by mixed models with fixed effect or ANOVA with repeated measures if the test prerequisites are satisfied (normality, homoscedasticity and sphericity).

Qualitative data will be compared with the Chi^2^ or the McNemar Test.

Correlation analyses will be performed with the Pearson Test. Logistic or multiple regressions will be performed to assess the effect of different variables on the outcomes: age, sex, body mass index, stage of renal disease, diabetes mellitus, MIS and CCI (either continuous or dichotomized) as well as biochemical data. A *p* < 0.05 will be considered statistically significant.

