**Methods:**

This is a case-control, prospective, interventional study. Inclusion criteria: age ≥ 60 years; CKD Stage 3b-5; clinical stability (i.e. no hospitalization and ≤ 25% in creatinine increase in the previous 3 months). Controls with normal kidney function will be matched in terms of age, gender and diabetes mellitus (requisite: estimated glomerular filtration rate ≥ 60 ml/min/1.73m^2^ available in the last 6 months). Exclusion criteria for cases and controls: neuromuscular disease, life expectancy < 3 months.

The handgrip strength protocol is an intermittent test consisting in 6 series of 9 repetitions of 3-s sub-maximum contractions at 40% of the maximum voluntary contraction (MVC) and 2 s of resting time between contractions. Each series is separated by one fast sub-maximum contraction and one MVC. Strength is assessed with a high-frequency handgrip dynamometer paired with surface electromyography. Symptoms of fatigue are assessed using MFI-20 and FACIT-F questionnaires. In order to reach a statistical power of 96%, we plan to enroll 110 subjects in each group.

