In the course of chronic dialysis, the loss of muscle function is worsened by several factors, such as acidosis, loss of amino acids (up to 12 g per hemodialysis session or 4 to 6 g per day on peritoneal dialysis) and/or the presence of anorexia. In this context, the loss of strength is mainly attributable to a decrease in muscle-mass, characterized by the loss, or a decrease in size, of the contractile units [25–27]. Conversely, changes in the excitation-contraction coupling system have been little explored and are poorly understood, especially in patients with advanced CKD.

The grip isometric analysis (i.e., handgrip) is the most commonly used test to assess strength in patients who have advanced CKD [28]. The handgrip test is simple and rapidly performed; it yields reproducible results and can easily be integrated into routine clinical practice. In CKD patients, this test demonstrates a close correlation with survival, nutritional status and quality of life [29–33]. Moreover, an isometric contraction is less traumatic than a dynamic contraction [34]. Finally, a handgrip is a simple routine gesture and does not usually cause pain.

Thus, the aim of the study is to assess the neuromuscular features of elderly patients with advanced CKD and symptoms of fatigue coupled with dynapenia. To our knowledge, this is the first study to apply a complex set of validated tests to a large population of elderly patients who have advanced CKD but are not on dialysis, with respect to an age, sex and diabetes matched control group. The research will highlight neuromuscular features associated with dynapenia in elderly CKD patients. In addition, the relationship between dynapenia and subjective fatigue will be analyzed to identify novel therapeutic interventions. These findings will be rapidly translated into clinical practice, with a view to adapting physical activity programs to improve neuromuscular function in the management of CKD symptoms.

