### Setting of study

The study will be carried out in Le Mans hospital (France), in the outpatient unit for the care of advanced kidney disease (UIRAV, Unité pour l’Insuffisance Rénale chronique AVancée). The UIRAV unit follows about 210 patients which are not on dialysis (90% over the age of 60), whose mean age is 74 years; 60% are males and diabetes mellitus prevalence is approximately 50%. Of these, 180 patients are followed for CKD Stage 3b-5. As previously described by Fois et al. [35], UIRAV’s main objective is to offer frequent follow-up and to delay the start of dialysis. The frequency of controls is based on CKD stage and overall clinical stability. For example, patients with stable kidney disease Stage 3b are seen every 8 to 12 weeks, while patients with CKD Stage 5 are seen at least once a month. Study proceedings is described in Fig. 1.

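### Controls are matched on age, sex and diabetes, but the named tests are unadjusted and unpaired for continuous outcomes and either unpaired or paired for binary ones, so the case-control comparison loses precision.

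*Protocol article*

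**What the plan says.** **Design.** The Methods part of the Abstract says "Controls with normal kidney function will be matched in terms of age, gender and diabetes mellitus". The Background presents the study as comparing CKD patients "with respect to an age, sex and diabetes matched control group". Neither place says whether matching is individual (1:1 pairs) or by frequency.

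**Tests.** Under Statistical analysis: "Group comparison for normally distributed variables will be assessed by means of the analysis of variance (ANOVA) or the unpaired Student T-Test". The rank tests named for non-normal data (Kruskal-Wallis, Mann-Whitney) are also independent-sample tests. Qualitative data go to chi-square "or the McNemar Test", with no rule for choosing.

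**Regressions.** The same section plans logistic or multiple regressions on the outcomes. The listed variables include age, sex, diabetes and stage of renal disease. Group (CKD versus control) is not in the list.

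**Power.** "With an 8% (±16%) difference", "accepting a 5% alpha risk", "96% statistical power will be reached by enrolling 110 CKD patients and 110 control subjects". The scale of the 8% and the 16% is not given. One of the two sources named for them is a set of reference values stratified by age and sex.

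**The concern.** The unpaired t-test treats the two groups as independent and unmatched, whereas McNemar presupposes 1:1 pairs. They imply different designs, and the article names no binary outcome measured twice in the same person that would explain McNemar otherwise.

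Matching makes the groups alike on factors related to strength. A test that omits those factors leaves their variance in the error term, so its standard error is too large for the design. The precision that matching should bring is then lost from the case-control comparisons: dynapenia prevalence between groups, which the Discussion expects to differ, and the continuous strength and fatigability measures. If controls are frequency-matched, McNemar cannot be applied, because no pairs exist.

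The power statement raises a related question: is its SD the one that the named test will meet? That depends on a scale the article does not give.

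**Working it through.** **Inputs from the article:** 110 per group, difference 8%, SD read as 16%, alpha 5% (two-sided assumed), stated power 96%; 60% men among the unit's patients (Setting of study). **Assumed, not in the article:** within-pair correlation ρ, and the women-to-men ratio of mean force r.

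**1. The plan's own figure.** For two independent samples, SE = 16 × √(2/110) = 2.157. Power = Φ(8/2.157 − 1.96) = Φ(1.748) = 0.960; the noncentral t with 218 df gives 0.958. The stated 96% reproduces as an unpaired two-sided calculation.

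**2. Unpaired test on matched data, SD 16%.** The true standard error is 2.157 × √(1 − ρ), but the test uses 2.157.
- Actual type I error = 2Φ(−1.96/√(1 − ρ)).
- Actual power of the unpaired test = Φ((8 − 1.96 × 2.157)/(2.157 × √(1 − ρ))).
- Confidence interval width relative to the matched analysis ≈ 1/√(1 − ρ).

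| ρ | Type I error, unpaired | Power, unpaired | Power, paired t | Relative CI width |
|---|---|---|---|---|
| 0 | 0.050 | 0.960 | 0.957 | 1.00 |
| 0.1 | 0.039 | 0.967 | 0.972 | 1.05 |
| 0.2 | 0.028 | 0.975 | 0.984 | 1.12 |
| 0.3 | 0.019 | 0.982 | 0.993 | 1.20 |
| 0.5 | 0.006 | 0.993 | 0.999 | 1.41 |

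For the planned difference the loss of power is about one percentage point at most. The main cost is intervals that are too wide. Under frequency matching with exact balance, the same formulas hold if ρ is replaced by the share of outcome variance that the matching factors explain.

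**3. Conditional case: 16% is a within-sex SD and the test is run on unstandardised force.** Set the men's mean to 1 and the women's to r, with 60% men and within-sex CV 16%. Only sex is considered here; age would add to it.
- Mean m = 0.6 + 0.4r.
- Within-sex variance W = 0.6 × 0.16² + 0.4 × (0.16r)².
- Total variance V = W + 0.24(1 − r)².
- The test's SE is 100√V/m × √(2/110). With sex exactly balanced, the true SE is 100√W/m × √(2/110).

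Example, r = 0.8: m = 0.92, W = 0.02191, V = 0.03151. The pooled CV is 19.3%, the test's SE 2.602 and the true SE 2.170. Power = Φ((8 − 1.96 × 2.602)/2.170) = Φ(1.337) = 0.909.

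| r | Pooled CV | Power if the balance on sex is disregarded | Power with sex balanced | Power adjusting for sex |
|---|---|---|---|---|
| 0.8 | 19.3% | 0.868 | 0.909 | 0.958 |
| 0.7 | 23.3% | 0.722 | 0.801 | 0.955 |
| 0.6 | 28.5% | 0.547 | 0.582 | 0.951 |

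The fourth column is the relevant one for a matched design. Adjustment for sex brings power back to about 95% to 96%.

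**The case against.** The strongest reply is that the sample size and the named test agree: 96% is what an unpaired test gives at SD 16%. Ignoring positive correlation makes the test conservative, so no excess of false positives arises. The primary objective under Aims is prevalence within CKD patients, which no two-group test affects. The regressions already list all three matching factors. Chi-square is consistent with the unpaired t-test, and a condensed article may list tests as a menu. All of this is fair and limits the size of the point.

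It does not remove it. The article does more than leave detail to another document: it names tests that do not fit the matching it describes, and a paired and an unpaired test for the same kind of data. The regressions are meant to assess the effects of listed variables, and group is not among them. Stage of renal disease could be coded with controls as a level, but the text does not say so.

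A reader might go further and infer that the comparison is on raw force, that the 16% cannot be achieved, and that true power is only 54% to 72%. The documents do not support this. No section says that the comparison uses raw force, and dynapenia is judged against an age- and sex-matched reference. Nor is the 16% said to be a within-stratum SD; a CKD cohort is its second source. The 54% to 72% also rests on assumed force ratios of 0.6 to 0.7 and disregards the balance on sex that matching creates.

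**Conclusion.** The point holds as one of efficiency and consistency. Continuous comparisons are named as unadjusted independent-sample tests in a matched design, and the treatment of binary data is undecided between unpaired and paired. At SD 16% and an assumed ρ of 0.1 to 0.5, type I error is about 0.039 to 0.006 instead of 0.05, and intervals are about 5% to 41% wider than a matched analysis would give.

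The 96% power is not refuted. A shortfall is only a conditional risk: if 16% is an SD within age and sex and the test is run on unstandardised force, power with sex balanced would be about 0.91 to 0.58 for an assumed force ratio of 0.8 to 0.6. Saying that the matching is ignored altogether would also be too strong, given McNemar and the planned regressions. The prevalence estimate in CKD patients is not affected.

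**What to change.** - Make the case-control comparison one pre-specified model per outcome, with group, age, sex and diabetes: a linear model for continuous outcomes, and for dynapenia a regression that gives a prevalence difference or ratio.
- State whether matching is individual or by frequency. If controls are paired 1:1, use the pair as stratum or random effect for all outcomes. If not, delete McNemar.
- State the scale of the 8% (±16%), for example percent of the age- and sex-specific reference or percent of mean force, so that the analysed outcome and the power calculation agree.

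The cost is wording only. Age, sex and diabetes are already collected, and no change in sample size or procedures is needed.

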## Methods

### Aims

The primary objective of this trial is to define the prevalence of dynapenia in elderly CKD Stage 3b-5 patients. This will be achieved through the analysis of handgrip strength.

The secondary objective is to define the characteristics of dynapenia in elderly patients with advanced CKD during a standardized task considering:
the evolution of MVC;the evolution of the discharge frequency of motor units;motor-unit recruitment ability;the evolution of the delay between the nervous stimulus and contraction;the relationship between dynapenia and subjective fatigue.

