#### Anthropometric, clinical, nutritional and biochemical data

Relevant data will be collected from medical records. They will include age, body mass index, gender, presence of diabetes mellitus (defined as glycemia > 126 mg/dl while fasting or using oral hypoglycemic medications or insulin) and kidney disease (i.e., cause and creatinine, urea and proteinuria values), time of follow-up, Charlson Comorbidity Index (CCI) [41], Malnutrition Inflammation Score (MIS) [42], albumin, total cholesterol, high-density lipoprotein, low-density lipoprotein, triglycerides, uric acid, calcium, phosphorus, parathyroid-hormone, vitamin D, bicarbonate, sodium and potassium values. The most recent available data will be recorded within 3 months for CKD patients and 6 months for control volunteers.

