### Inclusion criteria

#### Cases

Age ≥ 60Estimated glomerular filtration rate based on the Chronic Kidney Disease Epidemiology Collaboration (CKD-EPI) equation ≤45 ml/min/1.73m^2^ for at least 3 monthsStable clinical condition: no hospitalization; serum creatinine increased by a maximum of 25% in the previous 3 months

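### The secondary regressions name CKD stage rather than eGFR as the kidney-function term, although every case has a CKD-EPI eGFR; grouping gives up information on any gradient with kidney function

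*Protocol article*

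**What the plan says.** The Statistical analysis section of the protocol article plans logistic or multiple regressions for the effect of several variables on the outcomes. The list reads "age, sex, body mass index, stage of renal disease, diabetes mellitus, MIS and CCI (either continuous or dichotomized" and closes with biochemical data. Stage is the only kidney-function variable named there. The text does not say whether stage enters as a factor, as an ordered score or split in two, and it does not say whether these models are fitted in cases only.

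Three other places bear on the point:

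- **Inclusion criteria, Cases.** Eligibility rests on an estimated "glomerular filtration rate based on the Chronic Kidney Disease Epidemiology Collaboration (CKD-EPI) equation" of at most 45 ml/min/1.73m², so a continuous value exists for every case.
- **Anthropometric, clinical, nutritional and biochemical data.** The items collected include "kidney disease (i.e., cause and creatinine, urea and proteinuria values".
- **Aims.** The primary objective is to "define the prevalence of dynapenia in elderly CKD Stage 3b-5 patients". The secondary objectives concern the course of MVC, motor-unit behaviour, the delay between nervous stimulus and contraction, and the link between dynapenia and subjective fatigue. A gradient with eGFR is not among them.

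**The concern.** Stage is a coarse grouping of eGFR. With limits at 30 and 15, patients at 31 and 44 count as equal, while patients at 29 and 31 count as different. The value from which stage is derived is already held, so the grouping saves nothing.

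What is at stake is the chance of detecting that strength or fatigability worsens as kidney function falls within CKD. Among cases, that question has 110 patients behind it. The power stated for comparing cases with controls says nothing about it. If such a gradient exists and is moderate, a grouped kidney-function term makes it more likely to be missed.

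**Working it through.** **1. The plan's own figure.** The Statistical analysis section gives "With an 8% (±16%) difference, accepting a 5% alpha risk", and states that "96% statistical power will be reached by enrolling 110 CKD patients and 110 control subjects". Two-sided, with a standardised difference of 8/16 = 0.5:

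- z = 0.5 × √(110/2) = 3.708
- power = Φ(3.708 − 1.960) = Φ(1.748) = 0.960

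The 96% reproduces. It concerns cases against controls and does not involve stage or eGFR.

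**2. Inputs for a gradient among cases.**

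- From the document: n = 110 cases; eGFR at most 45; stages 3b, 4 and 5; threshold p < 0.05.
- Assumed, because the document gives none of them: stage limits 30 and 15; a linear effect on a continuous outcome such as MVC; correlation r = 0.20, 0.25 or 0.30 between eGFR and outcome; no other covariates; eGFR either uniform on 8 to 45 (A) or normal with mean 28 and SD 9, clipped to 8 to 45 (B).

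**3. Share of the explained variance that each coding keeps.** For A this can be done by hand, since the within-class variance of a uniform variable goes with the cube of the class width (15, 15 and 7 out of 37):

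- three-class factor: 1 − (15³ + 15³ + 7³)/37³ = 1 − 7093/50653 = 0.860
- cut at 30: 1 − (22³ + 15³)/37³ = 1 − 14023/50653 = 0.723
- ordinal score 1-2-3: squared correlation with eGFR = 0.852

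For B, computed numerically: factor 0.773, cut 0.646, ordinal 0.773. The shares in stages 3b/4/5 are about 41/41/19% in A and 41/51/7% in B.

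**4. Power.** With R² = r² × (share kept), the noncentrality is λ = 110 × R²/(1 − R²). It is referred to a noncentral F with 1 and 108 degrees of freedom, or 2 and 107 for the three-class factor. Example at r = 0.25: continuous eGFR has λ = 110 × 0.0625/0.9375 = 7.33 and power 76.5%. The factor under A has R² = 0.0625 × 0.860 = 0.0538, λ = 6.25 on 2 df and power 59.0%.

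| r | Continuous eGFR | Ordinal score (A / B) | Cut at 30 (A / B) | Three-class factor (A / B) |
|---|---|---|---|---|
| 0.20 | 56.4% | 49.7 / 45.9% | 43.4 / 39.5% | 39.8 / 36.1% |
| 0.25 | 76.5% | 69.3 / 64.9% | 61.9 / 56.8% | 59.0 / 53.9% |
| 0.30 | 90.5% | 85.0 / 81.1% | 78.3 / 73.3% | 76.9 / 71.7% |

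**5. Loss against continuous eGFR, over the three correlations and both distributions.**

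- ordinal score: 5.5 to 11.7 points
- cut at 30: 12.2 to 19.7 points
- three-class factor: 13.5 to 22.6 points

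**6. Sensitivity to the eGFR distribution.** Six other assumed shapes within 5 to 45 (two uniform, four truncated normal) widen these ranges to about 4 to 16, 12 to 35 and 12 to 27 points. The largest losses arise where one stage is nearly empty.

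**The case against.** The strongest reply is that the text does not exclude a continuous kidney measure. The variable list ends with biochemical data, and creatinine and urea are collected. The bracket about continuous or dichotomized form may cover the whole list or only MIS and CCI. Pearson correlations are also planned. All this stands, and it rules out the reading that the plan fixes kidney function as categorical only. It does not remove the point: eGFR is named on neither reading of the bracket, creatinine is not eGFR, and entering creatinine beside stage would put two overlapping kidney measures into one model.

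A second reply is that the coding of a covariate is detail for an analysis plan that is not shown. For the coding this is right. Naming stage rather than eGFR, however, is a choice that the article itself makes.

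Third, a reader might infer that the plan as written costs 12 to 23 points of power. The documents do not support that. The figure belongs to a factor or a cut at 30, neither of which is specified. An ordered score loses only about 5 to 12 points, and every figure rests on an assumed correlation, eGFR distribution and linear shape. Linearity favours continuous eGFR; a true threshold effect would narrow or reverse the difference.

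Fourth, a reader might treat the gradient as central evidence of the trial. The Aims list no such objective, and the expectations in the Discussion concern CKD against control, diabetes, electromechanical delay, and fatigue against fatigability.

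**Conclusion.** The point holds as a minor improvement to secondary analyses. Stage is the only kidney-function term named, a CKD-EPI eGFR exists for every case, and grouping it loses information. Under the assumptions listed in the working (110 cases, linear effect, r from 0.20 to 0.30, no other covariates, distributions A and B), the loss is about 5 to 12 points of power for an ordinal stage score, 12 to 20 for a cut at 30, and 14 to 23 for a three-class factor. These sizes illustrate what is at stake and are not properties of the plan, which fixes neither the coding nor an effect size. They apply to a continuous outcome; a logistic model for dynapenia was not computed. The primary prevalence estimate and the 96% power for the group comparison are untouched.

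**What to change.** In the regression sentence of the Statistical analysis section, replace stage by continuous CKD-EPI eGFR for the models fitted among cases. For example, report the effect per 10 ml/min/1.73m² and specify one check for non-linearity, such as an added quadratic term. Keep stage for descriptive tables.

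The cost is one phrase. No new measurement, visit or change of sample size is needed. Naming the variable in advance also removes the freedom to choose a coding after the results are seen.
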